## Abstract

**Background:**

Difficulty performing more than one task at a time (dual tasking) is a common and disabling problem experienced by people with Parkinson disease (PD). If asked to perform another task when walking, people with PD often take shorter steps or walk more slowly. Currently there is uncertainty about whether clinicians should teach people with PD to avoid dual tasking or whether they should encourage them to practice dual tasking with the hope that practice will lead to enhanced performance. This study will address this issue by comparing single to dual task gait training.

**Methods and design:**

A prospective randomised clinical trial is being conducted. Sixty participants with idiopathic PD will be recruited, provided they score I-IV on the modified Hoehn and Yahr (1967) scale, and fulfil other inclusion criteria. Participants will be randomly allocated to either a single or dual task gait training group. Both groups will receive 12 hours of walking training over 4 weeks. The single task group will undertake gait training with cueing strategies to increase step length. The dual task group will train to improve step length when walking and performing a variety of added tasks. Both groups will receive a tailored home program for 6 months. Blinded assessors will conduct four assessments: two baseline assessments, one post intervention and one at 6 months follow-up. The primary outcome measure will be step length when dual tasking over 8 m. Secondary outcome measures include: spatiotemporal gait parameters when walking under single and dual task conditions, measures of executive function, the timed up and go test, measures of community mobility, and quality of life. All analyses will be based on intention to treat principle.

**Discussion:**

This trial will examine the immediate and longer term effect of dual task walking training as compared to single task training in people with idiopathic PD, at the impairment, activity, and participation levels. It has the potential to identify a new intervention that may improve and maintain walking beyond the laboratory. The results of this trial will provide guidance for clinicians in the development of walking training programs for people with PD.

**Trial Registration:**

ACTRN12609000791235

## Background

Over 4 million people worldwide are estimated to be diagnosed with Parkinson disease (PD), with this projected to double within the next 20 years [1]. More than half of community dwelling adults living with PD experience gait disturbances that are associated with increased disease severity, disability, poor quality of life [2] and caregiver strain[3,4]. Falls are a common complication of PD, with between 50 and 68% of people with PD falling each year [5-8], with most falls reported to occur when walking [9]. Medications such as levodopa, provide the cornerstone of treatment of gait disturbances in PD, however these become less effective over time for some symptoms of PD including gait disturbance. There is growing evidence that strategy training, whereby internal or external cues are used to direct a person's attention to normalise their gait deficits, is effective in augmenting drug therapy to improve gait in the short term [10]. Internal cues involve the person directing their attention to consciously think of improving the deficit (e.g. thinking 'big steps'). External cues aim to normalise the gait deficit and often include verbal cues (e.g. saying 'big steps'), visual cues (e.g. lines on the floor at the desired step length) [11], or auditory cues (e.g. metronome to normalise cadence) [12]. The majority of this evidence is based on laboratory-based training [10] with low sample sizes, and measures of immediate effects of therapy. The longer term effect of strategy training is not yet clear.

For gait to be functional in daily life both within the community and home, people need to be able to dual task. This could involve thinking when walking or maintaining balance when holding an object. It is well known that performing an added task interferes with postural stability in older adults (termed dual task interference) [13], particularly in those adults with impaired balance [14-16].

It is well established that when asked to perform a concurrent task when walking, people with PD demonstrate reduced gait velocity, step length [11,17-20], increased stride to stride variability [21] and more freezing episodes [22,23] than when walking alone. These gait disturbances are also known falls risk factors [6]. An underlying rationale proposed for dual task interference in PD is that when required to perform two tasks at the same time, one runs through the frontal cortical regions and is under conscious control while the other is controlled by the defective basal ganglia. The task controlled by the frontal lobes is typically performed with normal speed and amplitude whereas the task controlled by the basal ganglia may show errors and be under-scaled in speed, amplitude and force [11].

Despite laboratory studies showing the serious effects of dual task interference on the spatiotemporal gait variables in PD, to date there have been few investigations of the effects of training on dual task interference during locomotion in PD. A pilot study of 90 minutes of multiple task training in 5 people with mild to moderate Parkinson Disease reported that participants reported low levels of fatigue, difficulty and anxiety and high levels of confidence [24]. A recent study has also demonstrated that people with PD can improve their ability to dual task when walking with training [25], however it only investigated the immediate effects of a 20 minute gait training session.

The primary aim of this randomised controlled trial (RCT) is to determine the short and longer-term effects of dual-task training compared to single task training during gait on walking performance when dual tasking in people with PD. In addition, we will determine the impact of the training programs on gait impairment, executive function, community mobility and quality of life.

## Methods

### Design

A prospective, single blinded two group randomised clinical trial with 6 month follow up of 60 people with PD living in the community setting will be conducted (Figure 1).

**Figure 1 F1:**
[figure not shown]
**Trial design**.

### Location and setting

We plan to recruit 60 people with PD, through Parkinson's Queensland Inc., a support organisation for people with PD, neurologists who specialise in Movement Disorders, and from the Queensland Parkinson's Project - a research study register of over 3000 community dwelling Queenslanders, recruited since 2005, who have agreed to participate in research into Parkinson's Disease and related disorders. Assessment will be undertaken at the Princess Alexandra Hospital, Brisbane, and training undertaken at St Andrew's War Memorial Private Hospital, Brisbane.

### Population

To be included in the study participants must meet the following criteria: (i) aged 18 years or older; (ii) a diagnosis of idiopathic PD using the UK Brain Bank criteria; (iii) able to walk 100 m independently with or without gait aids; (iv) rated stage I-IV on Hoehn and Yahr disability scale [26]; and (v) report reduced step length or slowed gait speed, confirmed by clinical examination. Participants will be excluded if they have neurological conditions other than PD, musculoskeletal or cardiopulmonary conditions that affect the ability to safely walk, had surgery for PD such as deep brain stimulation, score < 24 on the Mini-Mental Status Examination (MMSE) [27]; or sensory system pathology affecting walking or communication (e.g. blindness, deafness). All volunteers will be screened by a physiotherapist.

### Randomisation and blinding

Concealed randomisation will be prepared by an offsite investigator who is not involved in recruitment, intervention or data collection using a computer generated random number sequence. Consecutively numbered, randomly ordered opaque envelopes containing group allocation in 1:1 ratio will be opened consecutively after baseline assessment by the physiotherapists implementing the intervention.

Research assistants who enrol participants, and conduct pre, post and follow-up assessments will be blinded to group allocation throughout the study. Participants will not be informed of group allocation, however they may become aware of group allocation due to the nature of the intervention. Participant coding will not refer to group and participants will be instructed not to divulge information regarding their intervention to the research assistants undertaking the assessments. Treating physiotherapists will not be blind to group. To control expectancy effects for treating physiotherapists and patients it will be explained that it is not yet determined which therapy is more effective.

### Intervention

#### Single task training

Participants in the single task control group will participate in a 12-session program administered for 40-60 minutes each session, typically undertaken 3 times per week for 4 weeks. The intervention will be performed by a trained physiotherapist on a one-on-one basis, with training commencing at the patient's self-reported optimal 'ON' period, often 1 hour post medication. The single task group will receive an individually-progressed program of gait training aimed at improving step length via repeated practice of straight line walking, turning, obstacle negotiation and challenging gait tasks such as increasing speed and altering surface challenges. The classes will be performed in a hospital environment. A weekly guide for progression of task type and difficulty will be used. External cues to increase step length when walking will be used when needed and may include verbal, visual or auditory approaches. Participants will be instructed to concentrate on their walking performance during training. When training, care will be taken to ensure instructions are not performed when walking to avoid dual tasking during this intervention. A home program will be progressively integrated from week 2 with participants asked to continue with this program for 6 months. This will include a walking program, and a range of balance, strengthening and postural exercises particular to the patient, but chosen from a set of potential exercises. On completion of the intervention, participants will have a daily calendar in which to record their home program, and will receive monthly reminder follow-up telephone calls.

#### Dual task training

Participants in the dual task training group will also participate in a 12-session program administered for 40-60 minutes each session, typically undertaken 3 times per week for 4 weeks. As per the single task training group, the intervention will be undertaken by a trained physiotherapist on a one-on-one basis, with training commencing at the patient's self-reported optimal 'ON' period, often 1 hour post medication. The dual task gait training program will aim to improve step length under dual task conditions, that is, when concurrently performing added cognitive or motor tasks. Participants will undertake repeated practice of walking aiming to improve step length using external cueing techniques as outlined above, progressing to internal concurrent cueing of appropriate step length. The gait tasks undertaken will be progressed from simple to more complex tasks as outlined for the single task group.

In addition, a variety of added tasks will be progressively integrated into the training program. These include tasks such as listening, speaking, conversing, generation of simple and complex lists, language, calculation and motor tasks increasing in complexity. Tasks will include those designed to reflect functional everyday activities, such as carrying bags, getting keys out of a pocket, counting money, recalling directions or making a shopping list. Complexity will be progressively integrated as more complex tasks result in greater dual task interference with gait in people with PD [17,23,28,29]. Tasks involving maths and calculation will also be included as added language and calculation tasks can differentially impact gait performance in people with PD [20]. If able, participants will be progressed to performing increasingly complex cognitive tasks while concurrently walking. These may include visual spatial planning tasks (e.g. tell me how to get from here to reception), response inhibition tasks (e.g. complete the phrase without saying ...), or tasks integrating both language and calculation components (e.g. if Saturday is the 8^th^, what is the date the following Thursday?). Motor tasks such as carrying and manipulation will also be included as added tasks, as some studies have reported that added cognitive and motor tasks can both impact gait performance in people with PD [23]. These may be combined with cognitive tasks (e.g. getting a certain amount of money out of a wallet when walking). A weekly guide for progression of task type and difficulty will be used and programs will be individually-progressed.

Instructional set will commence with fixed priority training, whereby attention is equally shared between the walking and added task, but will aim to progress to variable priority training, whereby the proportion of attention directed to the gait and added task is varied from repetition to repetition [30]. For example, on one walking pass, a participant will be asked to concentrate mainly on taking big steps when also performing a counting task. In the next pass, they will be asked to concentrate mainly on the added task, trying to count as quickly and accurately as possible. Variable priority training has been shown to result in better balance during dual task gait conditions in older adults with balance impairment than fixed priority training [30], so this approach will be gradually introduced.

### Outcome measures

The primary outcome measure will be step length when dual tasking over 8 metres. Reduced step length has been shown to be one of the primary gait deficits in people with PD [31]. Participants will walk an unobstructed 10 metre path over an 8 metre GAITRite^® ^electronic walkway at a comfortable pace. At the same time, they will be asked to perform an added spoken task, including saying as many words as possible beginning with certain letters, termed the controlled oral word association test (words), or counting backwards by 3s beginning with a number between 50 and 100 (count). Both these tasks have been used to demonstrate altered gait in people with PD when dual tasking [20,25]. Step length is calculated by the GAITRite system, with the mean value used in analysis. The GAITRite^® ^system has demonstrated sensitivity to change in gait parameters in people with PD [32] and has been used as a gold standard comparator when investigating gait under dual task conditions in people with PD [33]. Assessment will be performed during the patient's self-reported optimal 'ON' period, often 1 hour post medication.

Secondary outcome measures include: spatiotemporal gait parameters when walking under single and dual task conditions, cognitive function, functional gait performance, community mobility, and quality of life. Spatiotemporal gait parameters other than step length will be recorded when walking at a comfortable pace over 10 metres under both gait only (single task) and the two dual task conditions detailed previously. These will include gait speed (m/s), cadence (steps/min), stride length (m), step length coefficient of variation (CV) and double support time (s).

Cognitive domains to be tested by a neuropsychologist include: executive function, attention, visual perception and processing speed. Tests have been selected based on their ability to assess the required domains, and their ability to detect deficits in the Parkinson Disease population [34]. Tests include the Trail making A & B Tests [35]; the Stroop colour-word interference test [36], and a Digit span test [37].

Functional gait performance will be measured using the Timed Up and Go (TUG) test with added motor and cognitive tasks [38]. Participants will be asked to walk as quickly as they safely can under all conditions and will be permitted to use their usual gait aid. A six minute walk test will be completed to quantify walking capacity. This test has demonstrated high reliability in people with PD (ICC = 0.95) [39].

Community mobility will be quantified using a questionnaire based on a self-report tool designed for community-dwelling older adults [40]. Activity will be measured over 3 days using an ActivPAL[41]. Health-related quality of life will be measured using a generic health-related quality of life measure, the EuroQuol (EQ-5D) [42] and the PDQ-39, which is specific to the Parkinson Disease population [43].

Several measures will be taken to characterise participants at each assessment session. Severity of PD will be categorised using the Hoehn and Yahr scale [26] and the Unified Parkinson's Disease Rating Scale (UPDRS) motor subsection III [44]. Freezing will be characterised using the Freezing of Gait questionnaire [45] and confidence will be measured using the ambulatory self confidence questionnaire [46]. General demographic information to be recorded will include: age, disease duration, medical history, number of falls in previous year, mobility aid use, medication type and dosage. Medication will be documented in detail at every assessment timepoint.

### Data analysis

Data analysis will be performed on an intention-to-treat basis using an alpha level of 0.05. Descriptive statistics will be used to ensure comparability of scores between groups at baseline, to describe performance at each phase and to test whether the assumptions for use of parametric statistics have been met. If the assumptions for F or t-tests are violated, equivalent non-parametric statistics will be utilized. The main hypothesis will be tested using General Linear Models (repeated measures analysis of variance, ANCOVA), in a 2 group (single task, dual-task) × 4 phase (baseline 1, baseline 2, post intervention, follow up) model. This will be followed by between-groups planned comparisons using the t-statistic. All secondary outcomes will be analysed in a similar manner. Disease duration and age will be used as co-variates in all analyses. Data will be analysed using SPSS.

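### The stated switch to unnamed non-parametric statistics makes the primary analysis depend on the trial's own data and sits badly with the covariate-adjusted group × phase model

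*Protocol article*

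**What the plan says.** All of this stands in the Data analysis section of the protocol article.

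- **The check.** Descriptive statistics will be used, among other purposes, "to test whether the assumptions for use of parametric statistics have been met".
- **The switch.** "If the assumptions for F or t-tests are violated, equivalent non-parametric statistics will be utilized".
- **The main test.** The main hypothesis is tested by repeated-measures general linear models "in a 2 group (single task, dual-task) × 4 phase (baseline 1, baseline 2, post intervention, follow up) model". Then: "This will be followed by between-groups planned comparisons using the t-statistic".
- **The covariates.** "Disease duration and age will be used as co-variates in all analyses".
- **The scope.** "All secondary outcomes will be analysed in a similar manner".

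The level is fixed ("using an alpha level of 0.05"). Sidedness is not stated, and I take it as two-sided. No diagnostic test, threshold or non-parametric method is named.

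**The concern.** The switch precedes the main-hypothesis sentence and applies to F and t-tests alike, so it governs step length when dual tasking, the primary outcome. Three things follow.

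1. The method for the primary outcome is chosen after looking at the data it will be applied to, among replacements that are not named.
2. The rank tests most people would reach for do not do the work of the planned model. Mann-Whitney compares two groups on one score. Friedman compares phases within one set of participants. Neither tests group × phase, and neither takes age or disease duration. Using them would drop the term that carries the hypothesis, contradict the covariate sentence, and give no adjusted mean difference with a confidence interval.
3. With four phases, sphericity is one of the F-test assumptions. Read as written, failed sphericity is a reason to leave the model, although a degrees-of-freedom correction deals with it inside the model.

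Secondary outcomes inherit the rule. Several are times or ratios that may well be skewed (Trail Making, Timed Up and Go, step length coefficient of variation).

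**Working it through.** **The plan's own figure.** The document attaches no number to the switch. Its only power figure is in the Sample size section: above 99% with 30 per group at Cohen's d above 5, and above 95% with 28 per group. At d = 5 both powers compute as 100%, so the figures reproduce. They do not bear on this point, because at d = 5 hardly any choice of test would matter. The calculations below use an assumed 0.5 SD difference.

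**How often would the switch occur?** The document gives no test or threshold. If formal 5% tests were used (an assumption):

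- Eight Shapiro-Wilk tests (2 groups × 4 phases) on perfectly normal data, if independent: 1 − 0.95⁸ = 33.7% of trials show at least one rejection. Simulation with correlated phases gave 29–33%.
- Adding Levene and Mauchly tests, with sphericity true: 45–49%.
- Normality judged only on pooled residuals, one test per phase: 15–18%.
- Mauchly alone, 60 participants: 4–5% with equal correlations between phases. It is about 45–100% with assumed correlations of 0.85–0.95 between baselines, 0.80 baseline to post and 0.70–0.75 baseline to follow-up.
- Lognormal data with log-SD 0.3–0.5: any of the tests rejects in 94–100%.
- Judged by eye: no rate can be calculated.

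**What would the switch cost?** Assume a 0.5 SD difference at post-intervention, 30 per group, baseline–post correlation r = 0.80, and correlation ρ between baselines of 0.85 to 0.95. Let m be the mean of the two baselines, and leave out age and disease duration. With outcome variance 1, the variance used by each analysis is:

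- Post score: 1.
- Change from m: 1 + (1 + ρ)/2 − 2r = 0.325 (ρ = 0.85) or 0.375 (ρ = 0.95).
- ANCOVA on m: 1 − r²/[(1 + ρ)/2] = 1 − 0.64/0.925 = 0.308, or 1 − 0.64/0.975 = 0.344.

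Approximate power is Φ(0.5/SD × √15 − 1.96). For Mann-Whitney on normal data the first term is multiplied by √(3/π) = 0.977.

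| Analysis | Formula | Simulation |
|---|---|---|
| t-test, post score | Φ(1.936 − 1.96) = 49% | about 47% |
| Mann-Whitney, post score | Φ(1.892 − 1.96) = 47% | about 45% |
| Mann-Whitney, change | Φ(3.320 − 1.96) = 91%; Φ(3.090 − 1.96) = 87% | 86–91% |
| ANCOVA on baseline | Φ(3.489 − 1.96) = 94%; Φ(3.304 − 1.96) = 91% | 90–93% |

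The normal approximation runs a point or two high at this sample size; otherwise the two columns agree.

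**Where the gap comes from.** From ANCOVA to Mann-Whitney on the post score the loss is about 45–48 points (90 − 45 to 93 − 45). Going from the t-test to Mann-Whitney on the same post score costs about 2 points (47 − 45). Nearly all the rest is the loss of the baseline.

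**Sensitivity.** A separate simulation put age and disease duration in the ANCOVA, with baseline–post correlation 0.6 / 0.8 and a 0.5 SD difference:

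- ANCOVA: 76% / 95%
- Mann-Whitney on post: 45% / 43%
- Mann-Whitney on change: 71% / 94%
- Rank-ANCOVA: 72% / 91%

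A rank method that keeps the baseline loses about 5 points or less. At 0.8 SD, Mann-Whitney on post has 83% at both correlations, and every baseline-using method has at least 98%.

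**Is non-sphericity a reason to leave the model?** The planned 2 × 4 interaction test with a Greenhouse-Geisser correction was simulated without age and disease duration, under five unequal-correlation patterns (the four behind the Mauchly range above and one with higher correlations to post and follow-up). Type I error was 4.3–5.8%. At 0.5 SD, power was 81–95% if the effect is present post-intervention only and 87–97% if it persists to follow-up.

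**The case against.** Much of the case on the other side stands.

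- **Non-parametric counterparts exist.** A reader might infer that none is available for this model. That is too strong: rank-ANCOVA, aligned-rank and non-parametric longitudinal factorial methods exist. A rank test on change is itself a group × phase contrast, and the planned t comparisons have a direct rank counterpart.
- **The text does not say that the covariates are dropped.** It requires age and disease duration in every analysis and nowhere prescribes unadjusted tests phase by phase. Dropping them is the likely result of the usual rank tests, not something the wording dictates. What the document shows is two sentences in tension.
- **The frequency is unknown.** A reader might infer that the switch would often be triggered. The document mentions only descriptive statistics and never names Mauchly's test. It does not give the interval between the two baselines, so the correlation pattern behind the 45–100% is assumed.
- **Ranks do not halve the power.** The fall to about 45% comes from ignoring baseline, which the quoted sentence does not require.
- **Detail may sit in an analysis plan not shown.** This is a fair answer to a missing threshold or test name, and neither is counted here. It does not answer the sentence itself: an analysis plan that kept the model in all cases would have to overrule it.

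What survives is that the protocol states a data-driven replacement of the primary model, leaves the replacement open, and applies it even to an assumption that the planned model can accommodate.

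**Conclusion.** The point holds in a limited form. The document fixes a rule under which the primary analysis changes with diagnostics on the outcome data. The usual reading of that rule conflicts with the covariate requirement in the same section and loses the interaction test.

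The harm runs from slight to large depending on a choice left open: under the assumptions above, power of 86–91% for a rank test on change or about 45% for one on the post score, against 90–93% for ANCOVA. These figures rest on an assumed 0.5 SD effect, assumed correlations and normal data. At the very large effect in the Sample size section the differences would vanish.

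Inflated type I error is another possible inference, and it has not been shown. Each procedure alone kept close to 5% in null simulations (4.6–5.9%), and the choose-after-looking procedure as a whole was not simulated. The objection is to an open choice of estimand and method, which is worth correcting because the correction is cheap.

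**What to change.** Replace the switching sentence with a rule that:

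1. keeps the covariate-adjusted group × phase model as the primary analysis whatever the diagnostics show;
2. handles non-sphericity by a Greenhouse-Geisser correction or by a mixed model with unstructured covariance;
3. names in advance any outcome to be log-transformed (Trail Making, Timed Up and Go and step length coefficient of variation are candidates);
4. for the primary outcome, makes any bootstrap, permutation or rank-based method a pre-specified sensitivity analysis that keeps the baseline, age and disease duration.

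The Greenhouse-Geisser option leaves the planned repeated-measures model as it is. The mixed model changes more and is not needed to settle this point. The cost is a few lines of text and slightly more programming, with no effect on sample size or data collection.

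### Both pre-randomisation baselines are modelled as outcome phases and baseline step length is not a covariate, so available precision may go unused

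*Protocol article*

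**What the plan says.** The abstract (Methods and design) plans "four assessments: two baseline assessments, one post intervention and one at 6 months follow-up". The Data analysis section puts all four into a repeated-measures general linear model that crosses the two groups with the visits, a "4 phase (baseline 1, baseline 2, post intervention, follow up) model". It continues: "This will be followed by between-groups planned comparisons using the t-statistic". The covariates are then fixed: "Disease duration and age will be used as co-variates in all analyses". The model carries the label ANCOVA, but those two are the only covariates named. Secondary outcomes are to be handled in a similar way.

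Under Randomisation and blinding, the envelopes "will be opened consecutively after baseline assessment by the physiotherapists implementing the intervention". I read this as after both baselines, so both are pre-randomisation values.

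The article does not say which term of the model tests the main hypothesis, or whether the t comparisons use raw scores or change from baseline. It gives no SD and no between-visit correlation for step length.

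**The concern.** The primary aim in the Background is the short-term and longer-term effect of one training programme against the other. That calls for a between-group difference at each of two post-randomisation visits. The described model does not deliver this directly:

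- **Group main effect.** It averages over two phases in which the true difference is zero, so it estimates only half of a sustained effect.
- **Group × phase interaction.** It has 3 degrees of freedom, one of them for baseline 1 against baseline 2, and gives no treatment difference at either time.
- **Between-group t comparisons.** These must supply the estimates. If they are made on raw scores at a phase, they ignore the participant's own baseline, which is likely to be the strongest predictor.

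At stake are the width of the reported intervals and their exposure to chance baseline imbalance in a trial of 60 people. Data the trial already collects could reduce both.

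**Working it through.** **Inputs from the protocol.** 30 per group; alpha 0.05 (two-sided assumed, as sidedness is not stated); two baselines and two later visits; covariates age and disease duration; the only standardised effect is Cohen's d above 5 (Sample size).

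**Assumptions.** Between-group difference d = 0.5 on the raw SD scale; compound symmetry with correlation ρ from 0.5 to 0.8; no contribution from age or disease duration.

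**1. The plan's own figure.** The noncentrality of a two-sample t-test is d·√(n/2). With d = 5 it is 5·√15 = 19.4 for 30 per group and 5·√14 = 18.7 for 28. Power is 1.000 in both cases, so the stated values (above 99% and above 95%) reproduce. Adjustment adds nothing to power at that effect size.

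**2. Variance factors, relative to a raw score at one visit.**
- Raw t: 1.
- Change from the mean of two baselines: 1 + (1+ρ)/2 − 2ρ.
- ANCOVA on the mean of two baselines: 1 − 2ρ²/(1+ρ).
- Group main effect over four phases: the effect is (0 + 0 + d + d)/4 = d/2 if sustained; the variance factor is (1+3ρ)/4.
- Group × phase F: 3 and 3 × 58 = 174 df. The noncentrality is (n/2)·d²/(1−ρ) for a sustained effect, and 0.75 of that if the effect is at post-intervention only.

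For the t-type tests, the noncentrality is the effect × √(n/2) / √(variance factor). For example, raw t gives 0.5·√15 = 1.94; ANCOVA at ρ = 0.7 gives 1.94/√0.424 = 2.97.

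**3. Power, d = 0.5, 30 per group.**

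| Test | ρ = 0.5 | ρ = 0.7 | ρ = 0.8 |
|---|---|---|---|
| Raw t at one visit | 0.48 | 0.48 | 0.48 |
| ANCOVA on mean baseline | 0.65 | 0.83 | 0.94 |
| t on change from mean baseline | 0.59 | 0.81 | 0.94 |
| Group × phase F, sustained effect | 0.61 | 0.85 | 0.96 |
| Group × phase F, effect at post-intervention only | 0.48 | 0.72 | 0.89 |
| Group main effect, sustained effect | 0.23 | 0.19 | 0.18 |

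**4. Interval width.** The ANCOVA residual SD factor is √(1 − 2ρ²/(1+ρ)): 0.816 at ρ = 0.5 and 0.537 at ρ = 0.8. Intervals are therefore about 18% to 46% narrower than for the raw comparison. This does not depend on d.

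**5. Chance imbalance.** The SE of the group difference in mean baseline is √[(2/30)(1+ρ)/2]: 0.224 SD at ρ = 0.5 and 0.245 SD at ρ = 0.8. The share passing into an unadjusted post-intervention difference is 2ρ/(1+ρ): 67% and 89%. An imbalance of one SE therefore shifts that difference by 0.224 × 0.667 = 0.15 SD to 0.245 × 0.889 = 0.22 SD.

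**The case against.** The strongest reply is that a 2 × 4 repeated-measures analysis is valid under randomisation, and that its natural test of treatment, the interaction, already compares within-person change. This stands. With a sustained effect and ρ of 0.5 or more, the interaction loses little or nothing against ANCOVA. It loses more if the effect is present only at post-intervention.

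A reader might infer that the planned comparisons lose about half their attainable power. The documents do not support that. It holds only for raw t-tests with d of about 0.3 to 0.5 and correlations of about 0.7 to 0.9, none of which the protocol gives. The text does not say that the t comparisons use raw scores. With correlations of 0.9 between baselines and 0.8 from baseline to post-intervention, a change-score t has power of about 0.90 against 0.915 for ANCOVA. Nor does the text make the group main effect the test of the hypothesis, or make the t comparisons conditional on a significant interaction.

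It is also tempting to say that baseline drift could produce a false positive interaction. Under the null, such results fall within the nominal 5% of a correctly sized F-test, so this is no validity flaw. Age and disease duration may recover part of the loss: if they explained 10% to 30% of the variance, power for the t comparison would be about 0.52 to 0.62.

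Finally, an article may leave the coding of contrasts to a full analysis plan. That is fair for the contrast. It does not cover the phases and covariates, which the article states.

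**Conclusion.** The point holds as an efficiency improvement, not as an error that invalidates the analysis. The text makes both pre-randomisation baselines levels of the outcome factor and names no baseline value of the outcome as a covariate.

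The cost ranges from almost nothing (change-score contrasts, or the interaction with a sustained effect) to a fall from 0.65–0.94 to 0.48 in power (raw comparisons at one visit). The latter range assumes d = 0.5, 30 per group, compound symmetry with ρ of 0.5 to 0.8, and no help from age or disease duration. At the protocol's d above 5 no power is lost, but the gains in interval width and in protection against imbalance over a raw comparison would remain.

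**What to change.** In Data analysis, make post-intervention and 6 months the only outcome occasions. Fit a linear mixed model, or ANCOVA at each occasion, with group, time, group × time, the mean of baselines 1 and 2 (and its interaction with time), age and disease duration. Report the adjusted between-group difference with its 95% CI at each time. Use baseline 1 against baseline 2 only to describe stability. Do the same for every secondary outcome that is measured at baseline.

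The cost is a change of wording. No new data are needed, and SPSS, the software already named, can fit the model.
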